### Assessment

#### Tumor response assessment

Baseline CT/MRI scan will be performed within 28 days prior to the first treatment. The second CT/MRI scan will be done before surgery. Baseline and the second assessment must follow the same radiological procedures, which include chest CT and abdomen CT/MRI. RECIST v1.1 is utilized for assessment of treatment response.

#### Safety assessment

Routine blood tests, liver and kidney function tests will be performed once a week during the first two weeks. Laboratory tests such as blood routine, liver and kidney function, troponin-T, serum cortisol, and adrenocorticotropic hormone will be performed (once every three weeks for the rest before operation) to evaluate the safety of the treatment. The dosage will be adjusted according to the instructions if the patients have any safety issues.

#### Follow-up

Within one year after the operation, imaging evaluations will be performed every 3 months which including contrast-enhanced CT/MRI of the upper abdomen and plain CT of the chest. In the second year after surgery, imaging assessments will be performed every 6 months until subjects experience disease progression. After progression, survival follow-up will be performed every 6 months. Due to the small sample size of this study, if there will be a loss of follow-up in the following process, it is necessary to supplement the sample size to ensure 20 enrolled people. Clinical visit information is detailed in **Table 4**.

**Table 4 T4:** Clinical visit information diagram.

	Screening period	Neoadjuvant Therapy(RT+ Sintilimab +Lenvatinib)			Operation			All eligible patients(Non-operated patients will be counted from the day of neoadjuvant failure and surgical patients will be counted from the first postoperative day)		
		Neoadjuvant therapy week 2 (during radiotherapy)	Neoadjuvant therapy week 4(before the start of cycle 2 of sintilimab)	Neoadjuvant therapy week 7(before the start of cycle 3 of sintilimab)	Before Operation	During Operation	1 month ± 10 days after operation	3 month ± 10 days	1st year every 3 months ±10 days	From 2^nd^ year, every 6 months ± 10 days until disease progression or death
Demographics	**√**									
Past medical history	**√**									
Vp typing of PVTT	**√**							**√**		
Child-Pugh score	**√**			**√**	**√**		**√**			
ECOG score	**√**			**√**	**√**		**√**	**√**	**√**	**√**
ICGR-15	**√**				**√**					
Routine blood test	**√**	**√**	**√**	**√**	**√**		**√**	**√**	**√**	**√**
Liver and kidney function test	**√**	**√**	**√**	**√**	**√**		**√**	**√**	**√**	**√**
Thyroid function test	**√**			**√**						
ACTH test (8:00 am.)	**√**			√						
Serum cortisol test (8:00 am.)	**√**			**√**						
Troponin	**√**		**√**	**√**						
AFP、PIVKA-II	**√**				**√**		**√**	**√**	**√**	**√**
immune-related biomarkers(PD-L1、TMB)							**√**			
Immune cell typing (CD4+ T cells, CD8+ T cells)	**√**				**√**		**√**			
Abdominal image	**√**				**√**		**√**	**√**	**√**	**√**
Lung imaging	**√**				**√**			**√**	**√**	**√**
ECG	**√**				**√**					
Inclusion and exclusion criteria judgment	**√**									
Neoadjuvant therapy		**√**	**√**	**√**						
Operation						**√**				
Efficacy evaluation				**√**				**√**	**√**	**√**
Adverse event		**√**	**√**	**√**	**√**	**√**	**√**	**√**	**√**	**√**
Concomitant medication/therapy		**√**	**√**	**√**			**√**	**√**	**√**	**√**

#### Sample size

The main study center treated 5 HCC patients with PVTT (all VP4) between 2020 and 2022. These patients underwent surgery after using the same neoadjuvant therapy as this trial. All patients achieved good efficacy, with a postoperative MPR of 60% (3/5), and manageable safety profile, supporting this trial. Based on this result, we set the end-point of effective response rate as 60%. We simulated response rates of 10%, 20%, and 30% assumed as pathological effective naturatly before intervention. The recruiting time for whole population of the patients is 24 months, and the last enrolled patient will be followed for 12 months. Two-sided Tests with 80% power is used with type I error set at 0.05, and one-Sample tests for exponential hazard rate is used to calculate sample size. The sample size calculate by PASS software 2021 version is 6, 10 and 18 for an effective response rate 10%, 20% and 30%, respectively. Based on the maximum possible effective response rate as control at baseline, we finally set it as 30% and obtained a sample size of 18 that included 11 events. The final sample size is 20 patients, allowing for a 10% loss to follow-up.

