**Methods:**

This open-label, single-arm, prospective, multi-center Phase I trial will enroll 20 HCC patients with PVTT who have a resectable primary tumor and no extra-hepatic metastasis. Eligible patients will be given radiotherapy, 3Gy*10 fraction, and will receive lenvatinib 8-12mg once daily and sintilimab 200mg once every three weeks. Surgical resection will be performed 6-8 weeks after radiotherapy. The primary endpoint is safety (number of patients ≥3G TRAE) and the number of patients who complete pre-op treatment and proceed to surgery. The secondary study endpoints include Major Pathological Response (MPR), 1-year tumor recurrence-free rate, Objective Response Rate (ORR), Imaging-Pathology Concordance Rate (IPCR), PVTT regression rate, Median Overall Survival (OS) and Recurrence Free Survival (RFS).

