**Discussion:**

This trial may confirm that surgical resection following intensive neoadjuvant therapy can provide a safe and efficient regimen for BCLC stage C patients with PVTT.

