#### Statistical analysis

This is an open-label, single-arm, phase I clinical trial and a planned 20 eligible subjects will be enrolled. Descriptive Analysis: The description of the quantitative indicator will give the median. Baseline Demographic Analysis: Descriptive analysis of baseline demographic data, and the chi-square test or survival analysis for numerical data in the experimental and control groups, depending on the data type. Analysis of evaluation indicators: Safety and feasibility, MPR rate, 1-year recurrence-free survival rate, ORR, PVTT regression rate, IPCR, ECOG score, tumor marker changes (AFP, PIVKA-II), ICG-R15 Changes, changes in liver function, etc. analysis of variance using two independent samples t-test, nonparametric test, repeated measures design according to data type. OS and RFS will use survival analysis according to data type. Safety evaluation: Adverse events will be described by the number and incidence, and detailed descriptions of the specific manifestations and degrees of all adverse events and their relationship with the drugs used. Since it is an exploratory study, the research data and results are subject to the investigator’s evaluation, and a Data Monitoring Committee (DMC) is not specially established.

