## Anticipated results

Safety and feasibility will be used as a primary endpoint, and MPR, one-year recurrence-free survival, ORR, IPCR, PVTT regression rate, OS and RFS will be as secondary endpoints. We expect to observe the safety data and the surgical conversion rate of the study group in order to assess the feasibility of subsequent phase II clinical study. And we will use these outcomes to determine the sample size of the further clinical study.

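### The only sample-size calculation uses rates from a secondary endpoint (MPR) in a hazard test, so its 80% power says nothing about primary safety or feasibility and does not hold for binary MPR either

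*Protocol article*

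**What the plan says.** The Methods paragraph of the abstract reads: "The primary endpoint is safety (number of patients ≥3G TRAE) and the number of patients who complete pre-op treatment and proceed to surgery". The Anticipated results section repeats the split: "Safety and feasibility will be used as a primary endpoint, and MPR, one-year recurrence-free survival, ORR, IPCR, PVTT regression rate, OS and RFS" are listed in that order, with everything from MPR onward secondary. That section also says the safety data and surgical conversion rate will be used to judge whether a phase II study is feasible.

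The Sample size section starts from five earlier patients "with a postoperative MPR of 60% (3/5), and manageable safety profile, supporting this trial". It continues "Based on this result, we set the end-point of effective response rate as 60" per cent. For the reference rate it says "We simulated response rates of 10%, 20%, and 30% assumed as pathological effective naturatly before intervention". The test is then specified: "Two-sided Tests with 80% power is used with type I error set at 0.05, and one-Sample tests for exponential hazard rate is used". With 24 months of recruitment and 12 months of follow-up after the last patient, it reports sizes of 6, 10 and 18 for the three reference rates. It chooses 30% (18 patients, 11 events) and arrives at 20 after allowing 10% loss.

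Outcome definitions gives both primary endpoints as counts of patients, and MPR as a yes/no result (at most 10% surviving tumour). In Statistical analysis, "Adverse events will be described by the number and incidence". The same section also puts safety and feasibility first in a list of indicators to be analysed by two independent samples t-test, nonparametric test or repeated measures methods.

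**The concern.** The stated alpha, power and N look like the justification for the trial, yet none of their inputs concerns the question the trial calls primary. The article gives no null value, target rate or precision for grade ≥3 toxicity or for reaching surgery. The tests listed for those endpoints need a second group or repeated measurements, and a single-arm trial with one yes/no result per patient has neither.

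At stake is the phase II judgement, which is to rest on the safety and conversion results. Unless the article says what 20 patients can show about those two proportions, raw counts may be read as firmer than they are.

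**Working it through.** **1. Reproduce the printed sizes.** Inputs from Sample size: rates of 60% versus 10%, 20% or 30%; two-sided 0.05; 80% power; accrual 24 months; total time 36 months; one-sample exponential hazard test. One assumption is needed: each rate is read as a 12-month event-free proportion S.

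- Hazard: λ = −ln(S)/12. For S=0.60, λ1 = 0.04257 per month; for S=0.30, λ0 = 0.10033.
- Events: d = [(1.960 + 0.842)/ln(λ1/λ0)]².
- Probability of an event under the alternative, uniform accrual: P = 1 − [exp(−12λ1) − exp(−36λ1)]/(24λ1) = 1 − (0.600 − 0.216)/1.0217 = 0.624.
- N = d/P.

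| Reference rate | λ1/λ0 | d | N | Rounded up | Printed |
|---|---|---|---|---|---|
| 10% | 0.222 | 3.46 | 5.55 | 6 | 6 |
| 20% | 0.317 | 5.96 | 9.55 | 10 | 10 |
| 30% | 0.424 | 10.68 (11 events) | 17.11 | 18 | 18 (11 events) |

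Loss: 18/(1 − 0.10) = 20. Everything matches. Of the hazard-test readings tried (rates as hazards, as 12-month event probabilities, or as 12-month event-free proportions), only this one gives 6, 10, 18 and 11 events together.

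**2. What the calculation is about.** The 60% is MPR in 3 of 5 operated patients, and the 30% is an assumed pathological response rate. No toxicity rate or rate of reaching surgery enters. On the reading that reproduces the figures, the 11 events are failures over time, not responders.

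**3. Does the 80% at least hold for MPR?** MPR is binary, so use an exact one-sample binomial test of 60% versus 30%, with upper tail at most 0.025.

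- N=18: P(X≥9 | 0.30) = 0.0596, too large; P(X≥10 | 0.30) = 0.0210, so the cut-off is 10. Power = P(X≥10 | 0.60) = 0.737.
- N=20: P(X≥10 | 0.30) = 0.0480, too large; P(X≥11 | 0.30) = 0.0171, so the cut-off is 11. Power = P(X≥11 | 0.60) = 0.755.

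That is 74% and 76%, not 80%.

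**4. What 20 patients give on the primary endpoints.** Power cannot be computed, because the article states no null or target. Precision can. Clopper-Pearson 95% intervals:

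| Count | Interval |
|---|---|
| 0/20 | 0% to 16.8% (upper limit 1 − 0.025^(1/20)) |
| 4/20 | 5.7% to 43.7% |
| 10/20 | 27.2% to 72.8% |
| 16/20 | 56.3% to 94.3% |
| 18/20 | 68.3% to 98.8% |

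The widest is 10/20, with half-width (72.8 − 27.2)/2 = 22.8 points.

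**The case against.** The strongest reply is that nothing false is said about the primary endpoints. The Sample size section speaks throughout of MPR and pathological response. A reader might infer that the plan claims 80% power for safety and feasibility, but the text never attaches it to them. The trial is described as exploratory phase I, where a descriptive primary aim, with N guided by an activity signal, is a legitimate choice. This stands, and it limits the point: the stated power is silent on the primary question, and the article does not say so.

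A reader might also infer that the primary endpoints receive nothing but counts. That is too strong, since Statistical analysis lists safety and feasibility for comparative tests. Those tests do not fit a single arm, so they supply no primary hypothesis.

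A third tempting reading is that the article promises proof of safety, because the abstract says "This trial may confirm that surgical resection following intensive neoadjuvant therapy can provide a safe and efficient regimen". The verb is hedged, and the Discussion section describes the expected evidence on safety and efficacy as preliminary. No change is needed there. Likewise, the surgery rate the Discussion quotes for another regimen is not used by this trial as a benchmark, so N=20 should not be judged against it.

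Finally, interval methods and denominators are often left to an analysis plan that is not shown. Their absence alone would be no finding. What remains is what the article does print: a powered N that does not concern the primary endpoints, and two-sample tests that cannot be applied to them.

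**Conclusion.** The point holds in this form. The N of 20 and its 80% power come wholly from MPR-based rates put through a time-to-event test. The power does not apply to safety or feasibility, for which no null, target or precision is stated. It also overstates the power for MPR as defined: 74% at 18 and 76% at 20 by an exact test.

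The size of the trial itself is not shown to be wrong. On the primary proportions, 20 patients give exact 95% intervals with a half-width of up to about 23 points. If no patient has a grade ≥3 treatment-related event, a true rate of up to 17% is still compatible with the data.

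Assumptions: the rates were read as 12-month event-free proportions to reproduce the printed sizes; the MPR power takes the protocol's 60% and 30% as given for every patient counted; the intervals use a denominator of 20. Follow-up provides for adding patients if some are lost, so the number enrolled could be slightly larger.

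**What to change.** Keep N=20.

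- **Sample size:** state that the calculation rests on MPR-based rates in an exponential hazard test, that its 80% power does not apply to safety or feasibility, and that exact power for MPR at 60% versus 30% is about 76% with 20 patients. Do not simply reassign the 80% to MPR. Then justify N=20 by precision on the primary proportions: exact 95% half-width at most about 23 points (10/20: 27% to 73%), and an upper limit of 17% if 0/20 have an event.
- **Statistical analysis:** for safety and feasibility, replace the two-sample and repeated-measures tests with the two proportions over all enrolled patients, each with a Clopper-Pearson 95% interval. The descriptive tabulation of adverse events stays.
- **Anticipated results:** say that the phase II judgement will be read against those intervals.

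The cost is a few sentences and two intervals, with no extra patients. The downside is that the stated power becomes less favourable.

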## Methods and analysis

### Study design

This is an open-label, single-arm, prospective, multi-center phase I trial in HCC patients with portal vein thrombus which will be conducted in 5 hospitals in China. (**Figure 1**). The study is being followed the Declaration of Helsinki and Good Clinical Practice. The protocol and its amendments have been approved by the ethics committee of Beijing Tsinghua Changgung Hospital (No. 21323-0-03). The recruitment started on December 01, 2022. The enrolment is estimated to complete in December 1, 2025.

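### Recruitment lasts 24 months in the sample size section but 36 months in the study design section; one must be wrong, although the planned 20 patients suffice under either within the stated method

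*Protocol article*

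**What the plan says.** In the protocol article, the Sample size section bases the calculation on a fixed timetable: "The recruiting time for whole population of the patients is 24 months, and the last enrolled patient will be followed for 12 months". The method is named in the same paragraph: "one-Sample tests for exponential hazard rate is used to calculate sample size", with the error rates given as "Two-sided Tests with 80% power is used with type I error set at 0.05". The target comes from five earlier patients, of whom three had a major pathological response (MPR): "we set the end-point of effective response rate as 60" per cent. Null rates of 10%, 20% and 30% were tried and gave 6, 10 and 18 patients. The section then concludes: "we finally set it as 30% and obtained a sample size of 18 that included 11 events". A 10% allowance for loss brings the total to 20.

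The Study design section gives calendar dates: "The recruitment started on December 01, 2022. The enrolment is estimated to complete in December 1, 2025". That is 36 months of enrolment. Nothing in the article connects the two statements or explains the difference.

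**The concern.** Both statements describe how long it takes to recruit the whole trial population, and they differ by 12 months. For many single-arm designs this would matter only for scheduling. Here the chosen method is a time-to-event one, in which the recruitment period and minimum follow-up fix the probability that a patient has an event, and so fix N. A reader cannot tell which timetable the trial follows, or whether 18 is the method's result for the trial as scheduled.

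The calendar is also unclear. With 24 months of recruitment, enrolment closes in December 2024 and the last patient's 12 months end in December 2025. With 36 months, enrolment closes in December 2025 and those 12 months end in December 2026. The article gives no separate end-of-study date to settle the matter, yet its overall survival definition censors surviving patients at the end of the study.

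**Working it through.** **Inputs.** From the Sample size section: two-sided alpha 0.05, power 80%, alternative 60%, nulls 10%, 20% and 30%, recruitment R = 24 months, follow-up of the last patient F = 12 months, loss 10%. From the Study design section: R = 36 months. One assumption is needed, because the article does not say at what time the percentages apply: they are treated as 12-month event-free proportions. Recruitment is taken as uniform.

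**Formulas.**
- Monthly hazard: h = −ln(S)/12
- Required events: d = (1.960 + 0.842)² / [ln(h1/h0)]²
- Event probability: P = 1 − [exp(−h1·F) − exp(−h1·(F + R))]/(h1·R)
- Patients: N = d/P, rounded up
- Power at a given N: Φ(√(N·P)·|ln(h1/h0)| − 1.960)

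**Step 1: reproduce the stated figures (R = 24).** h1 = −ln(0.60)/12 = 0.04257. For the 30% null, h0 = −ln(0.30)/12 = 0.10033, the hazard ratio is 0.424 and its logarithm is −0.857. Then d = 7.849/0.735 = 10.68, or 11 events. P = 1 − (0.600 − 0.216)/1.022 = 0.624. N = 10.68/0.624 = 17.1, rounded up to 18, and 18/0.9 = 20. For the 20% null, d = 5.96 and N = 9.55, rounded to 10. For the 10% null, d = 3.46 and N = 5.55, rounded to 6. All the stated figures are recovered.

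**Step 2: change only R to 36.** P = 1 − (0.600 − 0.130)/1.532 = 0.693. The formula for d contains no recruitment term, so it stays at 10.68.

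| Null | Events d | N, R = 24 | N, R = 36 |
|---|---|---|---|
| 10% | 3.46 | 6 | 5 |
| 20% | 5.96 | 10 | 9 |
| 30% | 10.68 | 18 | 16 |

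Allowing for loss, 16/0.9 = 17.8, rounded up to 18.

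**Step 3: power if the number is kept (30% null).** At N = 18, expected events are 18 × 0.624 = 11.2 with R = 24 (power 82%) and 18 × 0.693 = 12.5 with R = 36 (power 86%). At N = 20 with no loss, power is 86% and 89%.

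**Step 4: sensitivity to the reference time (30% null).** The hazards are rescaled by replacing 12 in h with the new time; d does not change. At 6 months, P is 0.847 (R = 24) and 0.888 (R = 36), so N is 12.6 and 12.0, both rounded up to 13. At 18 months, P is 0.484 and 0.554, so N is 22.1 and 19.3, rounded up to 23 and 20. Of the three times tried, only 12 months returns the stated 18. In each case the longer recruitment never raises N.

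**Step 5: the same comparison as a proportion.** An exact binomial test of 30% against 60%, with at most 0.025 in the upper tail:
- n = 18: reject at 10 or more responses; tail probability 0.021, power 0.737
- n = 20: reject at 11 or more; tail probability 0.017, power 0.755
- The smallest n reaching 80% is 23 (12 or more; power 0.836)

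No recruitment or follow-up time enters this calculation.

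**The case against.** The strongest reply is that nothing was miscalculated. Every figure in the Sample size section follows from that section's own inputs, which Step 1 confirms. The 24 months is a planning assumption, while the December 2025 date is described as an estimate and was written after recruitment had begun. A later projection that differs from a design assumption does not invalidate the design. If the date is really the end of follow-up, 18 is exactly right and only a label needs correcting. In addition, the primary endpoints are safety and feasibility counts, which this calculation does not drive, and the Follow-up section fixes enrolment at 20 by replacing patients who are lost.

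Most of this stands, and it limits the consequence. It does not remove the contradiction: the article never says that its timetable was revised, and the Study design sentence refers to enrolment, not follow-up.

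A reader might go further and infer that the trial is too small or that its sample size is wrong. The documents do not support that. Longer recruitment with the same minimum follow-up gives more events per patient, so the requirement falls. Nor do the 11 required events depend on the recruitment period.

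**Conclusion.** The point holds as an inconsistency in the timetable that reaches an input to the sample size. One of the two recruitment periods, 24 or 36 months, is wrong or out of date. The match between 24 + 12 months and the 36-month window suggests a mislabelled date, but the article cannot confirm this.

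The numerical effect is two patients: 18 against 16, or 20 against 18 with loss. It runs in the safe direction, with power at 18 rising from about 82% to about 86%. These figures rest on the unstated 12-month reference time, which is well supported because it recovers all three sample sizes and the event count, and on uniform recruitment. The conclusion that 20 is enough applies only within the exponential-hazard method. Treated as the binary response that the paragraph describes, the same 30% versus 60% comparison has about 74% power at 18 and 76% at 20, short of the stated 80%.

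**What to change.** State one recruitment period in the Study design and Sample size sections, together with the date on which the last patient's 12 months of follow-up end. If recruitment is 24 months, correct the enrolment date, or relabel December 2025 as the end of follow-up. If it is 36 months, put that figure in the Sample size section and restate either the required number (16, or 18 with loss) or the power at 18 (about 86%). In both cases name the time point to which the 60% and 30% refer, and keep 20 patients.

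If the comparison is instead meant as an MPR proportion, remove the recruitment and follow-up inputs from the calculation and report the exact binomial power for the planned number. The timetable would still have to agree between the two sections.

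The cost is a few sentences and one recalculation, with no additional patients.

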#### Outcome definitions

Safety: the number of patients who reported incidence of grade ≥3 treatment-related adverse events (according to CTCAE v5.0);Feasibility: the number of patients who complete pre-op treatment and proceed to surgery;Major Pathological Response (MPR): a reduction in the proportion of surviving tumors below a clinically significant cutoff (≤10% of surviving tumors);1-year recurrence-free survival: the proportion of all patients without HCC recurrence one year after liver resection;Objective Response Rate (ORR): the percentage of patients with complete response (CR) and partial response (PR) in all patients, and the response to treatment is based on the modified Response Evaluation Criteria in Solid Tumors (RECIST 1.1);Imaging-Pathology Concordance Rate (IPCR): the proportion of all patients with consistent PVTT regression on preoperative imaging and postoperative pathological PVTT regression assessment;PVTT regression rate: the proportion of patients with PVTT regression after treatment, divided into PVTT regression rate assessed by imaging and PVTT regression rate assessed by pathology;Median overall survival (mOS): the median difference (in months) between the date of study enrollment and the date of death due to any cause. Patients still alive at the end of the study will also be treated as censored, with the last known survival date as the last survival time;Recurrence-free survival (RFS): from radical resection to the date of the first documented tumor into recurrence or death from any cause, whichever occurred first.

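### The sample size takes its 60% and 30% from pathological response but uses a test for survival times, so n = 18, the 11 events and the 80% power do not describe an MPR comparison

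*Protocol article*

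**What the plan says.** The Sample size section starts from five patients treated earlier with the same regimen: "All patients achieved good efficacy, with a postoperative MPR of 60% (3/5), and manageable safety profile, supporting this trial". It continues: "Based on this result, we set the end-point of effective response rate as 60" per cent. The comparison rates of 10%, 20% and 30% are also described as rates of pathological effect.

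The method is then given as two-sided, 5% type I error and 80% power, and "one-Sample tests for exponential hazard rate is used to calculate sample size". Its time inputs are: "The recruiting time for whole population of the patients is 24 months, and the last enrolled patient will be followed for 12 months". The section reports 6, 10 and 18 patients for the three comparison rates. It chooses the last: "we finally set it as 30% and obtained a sample size of 18 that included 11 events". Allowing 10% loss brings this to 20.

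The Outcome definitions section describes "Major Pathological Response (MPR): a reduction in the proportion of surviving tumors below a clinically significant cutoff", with the cutoff at 10% or less surviving tumour. MPR is a secondary endpoint; under Anticipated results, "Safety and feasibility will be used as a primary endpoint".

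The Study design section gives a recruitment start of 1 December 2022 and says: "The enrolment is estimated to complete in December 1, 2025".

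**The concern.** The rates and the test belong to different kinds of endpoint. MPR is read once, on the specimen. The number of patients needed to distinguish 60% from 30% cannot depend on how long recruitment lasts or how long the last patient is followed. An exponential hazard test depends on both.

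A reader would take 18 patients, 11 events and 80% power as properties of the MPR comparison, and might take the 11 events to be expected responders. The article says its outcomes will be used to size a later study, so it matters that the endpoint behind this calculation can be identified.

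**Working it through.** **Inputs (Sample size section).** Target 0.60; comparison rates 0.10, 0.20, 0.30; two-sided 5%; 80% power; 24 months accrual; 12 months minimum follow-up; 10% loss. One input is assumed because the article does not state it: the percentages are 12-month event-free proportions.

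**1. Reproducing the plan's figures.** Yearly hazard h = −ln(S), so h1 = −ln(0.6) = 0.511.

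Required events: E = (1.960 + 0.842)² / [ln(h1/h0)]².

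Probability of an event under the 60% target, with uniform accrual over 2 years and at least 1 year of follow-up: P = 1 − (e^(−h1) − e^(−3·h1)) / (2·h1) = 1 − (0.600 − 0.216)/1.022 = 0.624.

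Patients: n = E/P, rounded up.

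| Comparison rate | h1/h0 | E | E/P | n | Plan |
|---|---|---|---|---|---|
| 10% | 0.222 | 3.46 | 5.55 | 6 | 6 |
| 20% | 0.317 | 5.96 | 9.55 | 10 | 10 |
| 30% | 0.424 | 10.68 (11) | 17.11 | 18 | 18, with 11 events |

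18/0.9 = 20, as stated. Every printed figure matches. In this calculation an event is a failure: 18 × 0.624 = 11.2.

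**2. Other readings.** None gives the full set.
- Response itself as the event: n = 3, 5, 11, with 8.82 events at 30%.
- Rates used directly as yearly hazards: n = 4, 10, 25.
- Step 1 with a one-sided test: n = 5, 8, 14.
- Two-sided binomial, score formula: n = 5, 9, 20, with no event count.
- Two-sided binomial, exact: smallest n of 6, 12, 23.

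The expected number of responders, 18 × 0.6 = 10.8, also rounds to 11, but none of the response readings yields 6, 10 and 18.

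**3. Power for MPR as a binary endpoint, 30% against 60%.** Exact binomial, upper tail at most 2.5%:
- n = 18: reject at 10 or more; tail 0.0210; power 73.7%.
- n = 20: reject at 11 or more; tail 0.0171; power 75.5%.
- 80% is first reached at n = 23 (12 or more; power 83.6%) and holds for every n from 25 up.

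Normal approximation, power = Φ[(√n × 0.30 − 1.960 × √0.21)/√0.24]:
- n = 18: Φ(0.765) = 77.8%.
- n = 20: Φ(0.905) = 81.7%.

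The z-test behind that approximation has the same upper rejection limits as the exact test, so its actual binomial power at n = 20 is also 75.5%.

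**4. Effect of the recruitment period.** 1 December 2022 to 1 December 2025 is 36 months. With 3 years of accrual in step 1, P = 1 − (0.600 − 0.1296)/(3 × 0.511) = 0.693 and n = 10.68/0.693 = 15.4, so 16 rather than 18.

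**The case against.** The strongest reply is that the arithmetic is sound and little depends on it. The figures are correct for a 12-month event-free rate, and at n = 18 that formula gives 82.0% power. The article defines a 1-year recurrence-free proportion as a secondary endpoint, which would fit. The study is a single-arm, exploratory phase I trial with safety and feasibility primary, and the article attaches no decision rule to MPR. At 20 patients the usual normal approximation exceeds 80%, and the Follow-up section says lost patients will be replaced to keep 20. Most of this stands. The fault is the pairing of endpoint and method, the shortfall is moderate, and no extra patients are called for. It does not rescue the text: the section attributes 80% power to 18 patients on rates taken from MPR, and neither method gives 80% there.

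A reader might infer more than the article supports:
- That the 11 events are recurrences or deaths, and that recurrence-free survival was the intended endpoint. The match shows which inputs probably went into the software. The section names no landmark and no event.
- That the 24 months are wrong because the Study design section implies 36. Since 24 + 12 = 36, those dates may loosely cover the whole study. The documents do not show which is right.
- That missing precision statements for the primary endpoints are a fault. A condensed article may leave these to the full protocol or analysis plan.

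**Conclusion.** The point holds as a mismatch between endpoint and method. The 18 patients, the 11 events and the 80% power are not properties of an MPR comparison of 60% with 30%. For MPR at two-sided 5%, power is 73.7% (exact) or 77.8% (approximate) at 18 patients, and 75.5% or 81.7% at 20.

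These figures assume that 60% applies to every patient in the denominator. The five earlier patients all had surgery, so a rate over all enrolled patients would be lower if some are not resected. The article gives no denominator for MPR.

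That the events are failures is an inference from the match of all the printed figures. The mismatch itself does not depend on it, because it stands on the article's own description of the rates and the test.

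**What to change.** Keep 20 patients and name the endpoint being sized, in one of two ways.

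(a) **MPR.** Replace the paragraph with a one-sample exact binomial statement. All 20 enrolled patients form the denominator, and those not resected count as non-responders. For 60% against 30% at two-sided 5%, the rejection limit is 11 or more of 20 and power is about 76%. Delete the event count, the accrual and follow-up inputs and the 80% figure.

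(b) **A 12-month event-free (recurrence-free) rate of 60% against 30%.** Say so, define the event, and support both rates with evidence other than MPR. The existing 18, 11 and 20 can then stand if 24 months of accrual is confirmed. With 36 months, the 18 becomes 16.

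In either case, state that n is not derived from the primary safety and feasibility endpoints. Reconcile the 24-month recruitment in the Sample size section with the December 2022 to December 2025 enrolment in the Study design section.

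The cost is rewording. Under (a) the stated power falls from 80% to about 76%; under (b) the sponsor must supply a justification for the two rates. Neither adds patients.
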